### Safety, adverse events and risk assessment

An adverse event is defined in the International Conference on Harmonisation (ICH) Guideline for Good Clinical Practice as ‘any untoward medical occurrence in a patient or clinical investigation subject administered a pharmaceutical product and that does not necessarily have a causal relationship with this treatment’. In this trial, any known breach of PHF security, accuracy and confidentiality, whether intentional or unintentional will be considered an adverse event. A serious adverse event will be considered to be where these breaches lead to physical or emotional harm, as perceived by the participant. All adverse events are adjudicated by the committee. Disclaimers are included in the p-PHF and e-PHF regarding the medical information, and users are cautioned that there is the possibility of error or inaccuracy. The disclaimer also states that the user’s professional and clinical expertise and judgment are required at all times when using the information contained in the PHFs. Adverse events data, including seriousness of the adverse event, is collected with every questionnaire and during retrievals.

### Methods: assignment of interventions

#### Sequence generation and allocation concealment

Subjects will be randomized to one of three arms using computer-generated random numbers. The allocation sequence is concealed as randomization is via a central telephone using an Interactive Voice Response System ((IVRS) maintained at a separate organization). Factors for stratification are: aged 60 to 74 years or over 75 years; private medical insurance or no private medical insurance and hospitalization in the previous 12 months or not. Once the study manager confirms eligibility and obtains informed consent, the study manager calls the IVRS and after entering the strata factors, is given the randomly assigned intervention by the IVRS.

#### Blinding

Once the subject is enrolled in the trial they will be allocated a unique subject identifier, which is a six-digit number without any other identifier (subject ID). Any further documentation associated with the subject will only be identified by this number. Only persons directly related with this trial will have access to the database or stored records. The nature of the intervention does not permit blinding of either trial participants or health-care providers. Therefore, there will be potential for bias in trial conduct and potential for ascertainment bias in the determination of important clinical outcomes and quality of life. To reduce clinical outcome ascertainment bias, a blinded IAC will be used to make the determination which out-of-hospital events are serious. The other primary outcomes, mortality and all overnight hospitalizations, are objective outcomes and are not subject to ascertainment bias. Data on all hospitalizations, same-day hospitalizations, 28-day readmissions and deaths are administrative outcomes, coded and collected by the clinical information systems of public and private hospitals within the state of NSW. Questionnaires that collect information on secondary outcomes are mailed to all trial subjects without any assignment identifiers. All statistical analyses unrelated to acceptability of PHF and compliance of use are masked to intervention allocation via a separate data set.

### Methods: statistical analysis plan

All analyses will include all subjects randomized regardless of whether or when they may have withdrawn from the study. Therefore, for the primary and secondary objectives, the analysis will follow intention-to-treat principles. However, a completer’s analysis which is a comparison based on random allocation of subjects with complete data at the end of the trial, will also be undertaken as well as an as-treated complier’s analysis, which is based on the actual intervention and for how long it was utilized. The completer’s analysis and the as-treated analyses are exploratory analyses only.

#### Hypotheses

The primary hypothesis is that addition of a patient-held PHF to usual care results in fewer important clinical events using a combined endpoint of deaths, overnight hospitalizations and serious out-of-hospital events compared to usual care. The secondary hypothesis is that addition of a patient-held PHF to usual care improves quality of life and health status.

#### Primary statistical analyses

There are two co-primary analyses because this is a three-arm, randomized controlled trial: e-PHF versus usual care and p-PHF versus usual care. Both analyses use the combined endpoint of deaths, hospitalizations (excluding day-only admissions) and adjudicated serious out-of-hospital events, and both use an adaptation of the Andersen-Gill formulation [43] of the proportional hazards model in order to capture possibly correlated events in the same subject. A robust variance estimate [44] will be used that takes into account the possibility of correlation of risk of multiple events within a subject by including an additional time-dependent covariate indicating whether the event was the first or subsequent event of its kind. The level of significance for each analysis is 0.025. This is an intention-to-treat analysis.

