#### Sample size and power calculations

Hospitalizations are likely to dominate events in the composite endpoint of hospitalizations (excluding day-only hospitalizations), serious out-of-hospital events and deaths. Therefore hospitalization data were used to power the study, with the aim to detect a 25 % reduction in hospitalizations. The sample size and power calculations for the study were based on the Fisher’s exact test, as this is a conservative analysis and enables use of the Australian Institute of Health and Welfare data (AIHW) [47] that indicate a yearly risk of hospitalization of 62 % for women and 78 % for men aged 66 to 69, and 80 % and 115 % for women and men aged 70 to 74, respectively, using hospital separation data from 2003 to 2004. The AIHW data are for all hospitalizations. This study excludes day-only hospitalizations in the composite endpoint, but includes serious out-of-hospital events and deaths. Overall, we estimated that at least 70 % of the subjects in the control arm would have at least one event (either an overnight hospitalization, a serious out-of-hospital event or death) throughout the 48-month duration of the trial. With these assumptions, 80 % power and a 0.025 level of significance, to detect a 25 % reduction in hospitalizations requires 158 subjects per arm for analysis by a Fisher’s exact test of proportions. In order to provide for the loss of power due to patients discontinuing (at the most conservative, assuming a 40 % non-differential dropout from the intervention arms), the trial requires 792 subjects, or 264 subjects per arm. Regarding local feasibility, in 2008 there were 11,421 unplanned admissions via the emergency department at our institution (St George Hospital) alone for patients aged 60 years or older. The entire study area of southern Sydney has several public and private hospitals.

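### Randomization is stratified by age group, private insurance and prior-year hospitalization, but the co-primary Andersen-Gill model as described names none of these factors; if they are prognostic and left out, some precision is lost

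*Protocol article*

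**What the plan says.** Under Sequence generation and allocation concealment, the article lists the strata: "Factors for stratification are: aged 60 to 74 years or over 75 years; private medical insurance or no private medical insurance and hospitalization" in the preceding year or not. That makes 2 × 2 × 2 = 8 cells. The study manager enters the factors when calling the voice-response randomization system (IVRS).

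Under Primary statistical analyses, in the part headed as the statistical analysis plan, there are two co-primary comparisons (each PHF against usual care), and "both use an adaptation of the Andersen-Gill formulation [43] of the proportional hazards model in order to capture possibly correlated events". A robust variance is specified, "including an additional time-dependent covariate indicating whether the event was the first or subsequent event of its kind". On alpha: "The level of significance for each analysis is 0.025". No stratification factor is named there.

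Covariate adjustment also appears under Other analyses (exploratory). Its list of subgroup covariates contains age, but neither insurance nor prior hospitalization.

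Under Sample size and power calculations, the trial is sized on an unadjusted comparison of proportions: "we estimated that at least 70 % of the subjects in the control arm would have at least one event", and "to detect a 25 % reduction in hospitalizations requires 158 subjects per arm for analysis by a Fisher’s exact test of proportions". The same section expects hospitalizations to make up most of the composite events.

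**The concern.** Stratified randomization removes chance imbalance on the stratification factors, so the treatment estimate varies less from trial to trial than under simple randomization. A variance computed without those factors still counts the between-stratum differences as noise. If the factors predict events, the reported standard error then exceeds the true spread of the estimator, confidence intervals are too wide and the tests fall below their nominal level. The precision gained at randomization does not reach the reported result.

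Prior-year hospitalization is the factor of most interest, since past admissions plausibly predict future ones and admissions drive the endpoint. Age probably matters too. The yearly hospitalization figures in the sample size section rise between the two age bands shown by 80/62 = 1.29 in women and 115/78 = 1.47 in men. Both bands lie inside the younger stratum and the figures are population data on all admissions, so they support the direction and not a value.

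**Working it through.** **1. The plan's own figure.** Inputs from the sample size section: control proportion p1 = 0.70; a 25 % reduction gives p2 = 0.70 × 0.75 = 0.525; power 80 %; alpha 0.025. The article does not say whether alpha is one- or two-sided; two-sided reproduces its number.

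n = [z(0.9875)·√(2p̄(1−p̄)) + z(0.80)·√(p1(1−p1) + p2(1−p2))]² / (p1−p2)², with p̄ = 0.6125

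= [2.2414 × 0.6890 + 0.8416 × 0.6778]² / 0.175² = 4.472 / 0.030625 = 146.0

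With continuity correction: (146.0/4) × [1 + √(1 + 4/(146.0 × 0.175))]² = 157.2, so **158** per arm. Exact two-sided Fisher power at 158 is 80.3 %. The article assumes 40 % dropout: 158/0.6 = 263.3, so **264** per arm and 3 × 264 = **792**. All three figures reproduce. None relies on covariate adjustment, so this point does not touch them.

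**2. What omission would cost.** The article gives no prognostic strength for any factor, so everything here is conditional on assumptions. Set-up: two arms of 264, blocked randomization within the 8 cells, four years of follow-up with no dropout, constant baseline rate, gamma frailty variance 0.8, and 2.3 events per control subject (about 70 % with at least one). Factor prevalences for age, insurance and prior hospitalization are 0.4, 0.5 and 0.5. Variance is subject-clustered and robust, with 4,000 replicates per setting. Adjustment means adding the three factors as covariates. Rate ratios (age / insurance / prior hospitalization):
- weak: 1.2 / 1.0 / 1.3
- moderate: 1.4 / 1.1 / 1.7
- strong: 1.6 / 1.2 / 2.2

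Under no treatment effect, without the factors and without the event-order covariate:

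| Strength | Mean reported SE | Empirical SD | SE / SD | Rejection rate (nominal 0.025) |
|---|---|---|---|---|
| weak | 0.0984 | 0.0985 | 1.00 | 0.028 |
| moderate | 0.1032 | 0.1004 | 1.03 | 0.018 |
| strong | 0.1104 | 0.1053 | 1.05 | 0.018 |

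The Monte Carlo error of a rejection rate is √(0.025 × 0.975/4000) = 0.0025, so 0.028 is compatible with 0.025. With the event-order covariate the SE/SD ratios are 0.0841/0.0844 = 1.00, 0.0880/0.0859 = 1.02 and 0.0940/0.0905 = 1.04.

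Power at a rate ratio of 0.75, without and then with the three factors:

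| Strength | No event-order covariate | Gain (points) | With event-order covariate | Gain (points) |
|---|---|---|---|---|
| weak | 72.3 % → 73.0 % | 0.7 | 69.9 % → 70.7 % | 0.8 |
| moderate | 68.0 % → 70.6 % | 2.6 | 64.1 % → 68.3 % | 4.2 |
| strong | 62.5 % → 68.5 % | 6.0 | 57.4 % → 66.0 % | 8.6 |

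In the last pair of columns the mean reported SE falls from 0.0861 to 0.0855, 0.0899 to 0.0876 and 0.0955 to 0.0908, that is by about 1 %, 3 % and 5 %.

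**3. Reading these numbers.**
- The empirical SD hardly moves on adjustment (strong case, null, no event-order covariate: 0.1053 against 0.1050). Adjustment mainly lets the reported SE show precision that stratified randomization has already delivered.
- The 8.6-point gain is somewhat flattering. In that setting the estimate also shifts (−0.231 to −0.241), and the adjusted null rejection rate was 0.031 against 0.020 unadjusted.
- The absolute power levels reflect the assumed frailty and are no check on the trial's 80 %.
- With non-prognostic factors (158 per arm, 2,000 replicates) the ratio of unadjusted to adjusted SE was 1.00: nothing lost.
- Separate runs with prior-hospitalization rate ratios of 1.5, 2 and 3 gave power gains of about 2, 3–5 and 7–8 points. At 3 the SE overstatement was larger (0.105 against an SD of 0.097, about 8 %). Those runs are not shown to include the event-order covariate and state no prevalence for prior hospitalization, so they are not used for the range.

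**The case against.** The strongest reply is that this is a condensed article whose full analysis plan is not shown, and that handling of stratification factors is commonly left to that plan. The model description does not claim to list every term; even the treatment term is implicit. The exploratory list proves nothing about the primary model.

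Much of this stands. A reader might infer that the plan excludes the factors and that power is certainly given away. The text supports neither: it is silent on the factors, and the loss disappears if they are not prognostic. A reader might also infer that the tests are invalid or the trial wrongly sized. They are not: any error is conservative, and the sample size rests on an unadjusted test. Nor does this point support dropping the event-order covariate; whether to keep it is a separate question not argued here.

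What the reply does not remove is that the section presents itself as the statistical analysis plan and goes as far as naming a post-randomization covariate. At that level of detail, the factors used to randomize are a notable omission, and a model fitted exactly as described would leave them out.

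**Conclusion.** The point holds as one of efficiency and clarity. The randomization uses three factors and the co-primary model as described names none of them. If they are omitted and matter, the reported standard error is about 0 to 5 % too large and about 1 to 9 points of power are lost in each co-primary test. Both ranges rest on assumed rate ratios (up to 2.2 for prior hospitalization), prevalences and frailty; a population with few or nearly all subjects hospitalized in the previous year would give different values. Type I error is not inflated, and 158, 264 and 792 stand.

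The age strata also carry a definite wording gap. Read literally, a subject aged exactly 75 belongs to neither group, although the inclusion criteria admit anyone of 60 or more.

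**What to change.** Add one sentence to Primary statistical analyses: both co-primary Andersen-Gill models are stratified by, or adjusted for, age group, private insurance and hospitalization in the previous 12 months, as entered at the IVRS call, with subject-clustered robust variance. Either form serves. With 2 × 264 = 528 subjects per comparison and 8 cells, the average is 66 subjects per cell.

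Reword the age strata so that 75 falls in one of them, for example 60–74 and 75 or over, matching what the IVRS actually applied.

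The cost is wording only: the values are already captured at randomization, and the sample size does not change. If the full analysis plan already includes the factors, the article's description need only be brought into line with it.

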### Outcomes

#### Primary outcome

The primary outcome is a combined endpoint of the total number of important clinical events, defined as: all overnight hospitalizations, all serious out-of-hospital events and death. Validation of hospitalizations or out-of-hospital events occurs by subject interview, and health-care provider and hospital records as close to real time as is possible. In addition, record linkage with Medicare Australia, Department of Veterans Affairs, Australian Institute of Health and Welfare and NSW Health during the study is another source of valid information on hospitalizations, health service utilization (including a record of all medical encounters) and deaths. Furthermore, an Independent Adjudication Committee (IAC) determines which out-of-hospital events are serious, and are therefore included in the primary combined outcome.

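### Both co-primary models adjust for first versus subsequent event, a post-randomization variable, so the arm coefficient does not estimate the effect on total events and shrinks toward 1 under plausible conditions

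*Protocol article*

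**What the plan says.** Under *Primary outcome* the protocol article states: "The primary outcome is a combined endpoint of the total number of important clinical events". Under *Hypotheses* it states: "The primary hypothesis is that addition of a patient-held PHF to usual care results in fewer important clinical events". The target is thus the effect of a PHF on the whole event count.

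Under *Primary statistical analyses* there are two comparisons, each PHF arm against usual care. On the model, the section says: "both use an adaptation of the Andersen-Gill formulation [43] of the proportional hazards model in order to capture possibly correlated events in the same subject". The text continues: "A robust variance estimate [44] will be used that takes into account the possibility of correlation of risk of multiple events within a subject", and it says this is achieved "by including an additional time-dependent covariate indicating whether the event was the first or subsequent event of its kind". It adds that "The level of significance for each analysis is 0.025" and labels the analysis intention-to-treat. It describes no version of the primary model without the covariate.

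**The concern.** The sentence runs two separate devices together. A sandwich variance clustered on subject allows for correlated events by itself, without any extra covariate, and leaves the arm coefficient unchanged. A first/subsequent indicator changes what the arm coefficient means.

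Whether a subject has already had an event is a result of the process that the PHF is meant to alter. Conditioning on it does two things:

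- **Selection.** When subjects differ in underlying risk, usual-care subjects who are still event-free have withstood a higher rate and are on average lower-risk than event-free PHF subjects. Within each level of the covariate the randomized arms are no longer comparable.
- **Blocked pathway.** If a first event raises the risk of later ones, part of the benefit acts by preventing the first event. The covariate removes that part.

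Both move the hazard ratio toward 1 relative to the effect on total events. At stake are the size and meaning of both co-primary estimates and the position of their intervals.

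**Working it through.** **1. The plan's own sample size.** *Sample size and power calculations* assumes that "at least 70 % of the subjects in the control arm would have at least one event", and that "80 % power and a 0.025 level of significance, to detect a 25 % reduction in hospitalizations requires 158 subjects per arm".

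- Proportions: 0.70 and 0.75 × 0.70 = 0.525; difference δ = 0.175; mean 0.6125.
- With two-sided 0.025 (z = 2.2414) and 80 % power (z = 0.8416): n = [2.2414·√(2·0.6125·0.3875) + 0.8416·√(0.70·0.30 + 0.525·0.475)]² / 0.175² = 146.0.
- Continuity correction: n′ = (146.0/4)·[1 + √(1 + 4/(146.0·0.175))]² = 157.2, so 158. Exact Fisher power at 158 per arm is 80.3 %.
- Dropout: 158/(1 − 0.40) = 263.3, so 264 per arm; 3 × 264 = 792.

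The stated figures reproduce. They rest on a test of proportions, so the covariate does not enter them.

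**2. Inputs for the covariate's effect.**

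- From the protocol: 48 months (T = 4 years), 70 % of controls with at least one event, 264 per arm, 0.025 per comparison.
- Taken as the true effect: a rate ratio of 0.75, matching the planned 25 % reduction.
- Assumed, not in the documents: subject risk Z is gamma with mean 1 and variance θ from 0 to 2; constant rates; one event type, so the protocol's distinction by kind of event collapses to one kind.

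**3. Why selection occurs.** Let μ be the expected events per subject by time t in an arm. Then

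- P(no event) = (1 + θμ)^(−1/θ)
- E[Z | no event] = 1/(1 + θμ)

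Take θ = 1. Control: 1/(1 + μ) = 0.30, so μ = 2.333. PHF: μ = 0.75 × 2.333 = 1.75. At 48 months the mean risk among event-free subjects is 1/3.333 = 0.300 (control) and 1/2.75 = 0.364 (PHF). The rate ratio within that level is 0.75 × 0.364/0.300 = 0.91. Among subjects with a prior event the mean risk is 1 + 1/(1 + μ), that is 1.300 and 1.364, and the ratio is 0.75 × 1.364/1.300 = 0.79. Both are nearer 1 than 0.75.

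**4. Large-sample value of the planned estimate.** The Cox score equations for arm and prior-event status, solved with these expectations over 0 to 4 years, give:

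| Frailty variance θ | Planned model HR | Share of log HR lost |
|---|---|---|
| 0 | 0.750 | 0 % |
| 0.1 | 0.757 | 3 % |
| 0.25 | 0.767 | 8 % |
| 0.5 | 0.781 | 14 % |
| 1 | 0.798 | 22 % |
| 2 | 0.805 | 25 % |

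Share lost = 1 − ln(HR)/ln(0.75); for θ = 1, 1 − 0.2257/0.2877 = 0.22. With a true ratio of 1 the limit is exactly 1 at every θ. Without the covariate the limit is 0.750 throughout.

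**5. Simulation check (30,000 per arm, standard error of the log HR about 0.01).**

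| Scenario | With covariate | Without |
|---|---|---|
| θ = 0, independent events | 0.745 | 0.745 |
| θ = 0.5 | 0.773 | 0.743 |
| θ = 1 | 0.788 | 0.738 |
| θ = 2 | 0.806 | 0.747 |
| θ = 1, with deaths | 0.810 | 0.762 |
| θ = 0, first event multiplies later risk by 1.5 | 0.757 | 0.733 |
| θ = 0, first event multiplies later risk by 2 | 0.749 | 0.705 |

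The last two rows isolate the blocked pathway: the covariate leaves roughly the direct 0.75 and drops the further gain.

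**6. Test behaviour at 264 per arm.**

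- Rejection with no effect: 0.015 to 0.025 with the covariate, against a nominal 0.025.
- Power without and with the covariate, 800 replicates: 79 % and 77 % (θ = 0.5), 69 % and 65 % (θ = 1), 52 % and 47 % (θ = 2).
- A separate 400-replicate run: 77.2 % and 75.0 % (θ = 0.5), 66.7 % and 63.0 % (θ = 1), and 91.7 % and 92.0 % with 1.5-fold event dependence and no frailty.
- Interval at θ = 1: bias ln(0.798/0.75) = 0.062, standard error 0.0865, so 0.062/0.0865 = 0.72 standard errors. Coverage of the nominal 97.5 % interval for the effect on total events is Φ(1.52) − Φ(−2.96), about 93 %.

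**The case against.** Models with event history as a covariate are an established use of the Andersen-Gill framework, and the protocol openly calls its model an adaptation. Such a model validly estimates an effect conditional on prior events. That stands: the model is legitimate for a different question. The fault is its mismatch with the stated outcome of total events.

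A reader might infer that the primary test is invalid, or that the trial could falsely claim a benefit. The calculations do not support this. With no effect the hazard ratio is 1 and rejection does not exceed the nominal level, so the distortion is conservative. A reader might also infer a serious loss of power; the loss is about 0 to 5 points, and none was seen under event dependence alone.

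The size depends on a variance that the documents do not give. This also stands: at variance 0.1 only 3 % of the log hazard ratio is lost. Some difference in risk is hard to doubt among subjects aged 60 or over with varied chronic diseases, but its amount is unknown.

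Finally, the calculation uses one event type, whereas the covariate distinguishes events by kind and the composite includes death. The protocol expects hospitalizations to dominate and serious out-of-hospital events to be rare, so the direction should hold, but the figures approximate the specified model.

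**Conclusion.** The plan is wrong as written, with moderate severity. The covariate makes each co-primary arm coefficient conditional on post-randomization event history, so it does not estimate the effect on the total number of events. Attenuation is not automatic: it needs a true PHF effect together with differing subject risk or event dependence. The protocol itself allows for correlated events within a subject, which is the situation in which the problem arises.

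Under the stated assumptions a true 25 % reduction would be reported as about 25 % (no heterogeneity) down to about 19 to 20 % (variance 2: 1 − 0.805 = 0.195). The harm lies in the estimate and its interval, not in the validity of the test.

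**What to change.** In *Primary statistical analyses*, delete the first/subsequent covariate from the primary model. Specify the marginal Andersen-Gill rate model with randomized arm and a sandwich variance clustered on subject, and say that the clustering is what allows for within-subject correlation. Adding the baseline stratification factors is optional and not needed to cure this fault. If the prior-event model is wanted, keep it as a labelled sensitivity or exploratory analysis and describe its estimate as conditional on event history.

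The cost is about one sentence of analysis text. No further data are needed, and 158, 264 and 792 stand.

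### Testing each co-primary comparison at a fixed 0.025 is valid but avoidably conservative; Holm's step-down keeps the same implied 5 % family-wise error and is never less powerful

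*Protocol article*

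**What the plan says.** The protocol article, section *Primary statistical analyses*, sets up two tests that share the usual-care arm: "There are two co-primary analyses because this is a three-arm, randomized controlled trial: e-PHF versus usual care and p-PHF versus usual care". It then gives the threshold: "The level of significance for each analysis is 0.025". It describes no step-down and no passing of unused alpha from one test to the other.

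The section *Sample size and power calculations* uses the same threshold, "80 % power and a 0.025 level of significance". It assumes that "at least 70 % of the subjects in the control arm would have at least one event" and states that "to detect a 25 % reduction in hospitalizations requires 158 subjects per arm" "for analysis by a Fisher’s exact test of proportions". After "assuming a 40 % non-differential dropout from the intervention arms", it concludes that "the trial requires 792 subjects, or 264 subjects per arm".

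The article names neither a family-wise error rate nor the sidedness of the tests. A 5 % family-wise level is implied by 2 x 0.025, and two-sided testing is what reproduces the sample size (see the working).

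**The concern.** The trial has three arms so that both formats get an answer. The Discussion explains that the electronic file alone is not enough and that the paper file anchors the comparison. The two formats are described as similar in content, so a world in which both work is plausible, and that is where a single-step split loses most.

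Suppose one format gives p = 0.001 and the other p = 0.04. Under the fixed rule the second comparison is not significant, and the trial would be read as showing that one format works and the other does not. Control of family-wise error at 5 % does not require that verdict.

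**Working it through.** **1. Reproduce the plan's own figure.** Inputs from *Sample size and power calculations*: control proportion 0.70; 25 % relative reduction, so 0.70 x 0.75 = 0.525; power 80 %; alpha 0.025, taken as two-sided (z = 2.2414 and 0.8416).

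- Mean proportion = (0.70 + 0.525)/2 = 0.6125; difference d = 0.175.
- Uncorrected n = [2.2414 x √(2 x 0.6125 x 0.3875) + 0.8416 x √(0.70 x 0.30 + 0.525 x 0.475)]² / 0.175² = (1.5443 + 0.5704)² / 0.030625 = 146.0, or 147 rounded up.
- Continuity-corrected n = (146.0/4) x [1 + √(1 + 4/(146.0 x 0.175))]² = 157.2, rounded up to **158**, as stated. One-sided variants at 0.025 give 121 or 132, so two-sided is the reading that fits.
- Exact two-sided Fisher power at 158 per arm is 80.3 %.
- Dropout: 158/(1 - 0.40) = 263.3, rounded up to **264**; 3 x 264 = **792**.

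The threshold and the sizing therefore agree.

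**2. Holm has the same error bound.**

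- Both nulls true: any rejection needs the smaller p-value to be at most 0.025, which has probability at most 2 x 0.025 = 0.05.
- One null true: a false rejection needs that p-value to be at most 0.05, which has probability at most 0.05.
- Neither step uses independence, so the shared control arm is no obstacle.
- Under the global null the two rules have identical family-wise error: 3.4 % with Fisher at 158 per arm, 4.65 % with the normal test.

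**3. Power.** Write A for p ≤ 0.025 in one comparison and B for p ≤ 0.025 in the other. Holm rejects the first when A occurs, or when B occurs and the first p-value lies between 0.025 and 0.05. The chance of rejecting both is the sum of the two single powers minus the chance of at least one. Exact enumeration of two Fisher tests sharing one control arm (control proportion 0.70) gives, fixed split → Holm:

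| Per arm | True reductions | Power per comparison | Power for both | At least one (either rule) |
|---|---|---|---|---|
| 158 | 25 % and 25 % | 80.3 % → 85.2 % | 68.9 % → 78.7 % | 91.7 % |
| 264 | 25 % and 25 % | 96.6 % → 98.0 % | 93.9 % → 96.7 % | 99.3 % |
| 158 | 25 % and none | 80.3 % → 80.4 % (effective format) | not applicable | 80.9 % |
| 158 | 25 % and 15 % (assumed) | weaker format 34.3 % → 44.1 % | 32 % → 43 % | 82.4 % |
| 264 | 25 % and 15 % (assumed) | weaker format 58.0 % → 68.2 % | 57 % → 68 % | 97.1 % |

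Check on the first row: 2 x 85.2 - 91.7 = 78.7. The chance of a split verdict when both formats work is 91.7 - 68.9 = 22.8 % under the fixed split and 91.7 - 78.7 = 13.0 % under Holm.

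A bivariate normal simulation with exactly 80 % power per comparison and correlation 0.5 gives close agreement: each 80.0 % → 84.6 %, both 68.8 % → 77.9 %, at least one 91.3 %.

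**4. What Holm costs.** Suppose one format works and the other has no effect. The two-sided chance of a false rejection for the ineffective one then rises, in the normal model, from 2.5 % to 4.2 % when the effective format has 80 % power, and to 4.8 % when it has 96.6 %. With Fisher it goes from 1.8 % to 3.2 % at 158 per arm.

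**The case against.** The strongest reply is that nothing here is wrong. The split controls error, matches the sample size, and gives each comparison its planned power. That stands. A reader might infer from the power figures that the multiplicity rule is faulty or the trial under-sized. The documents do not support this: 158, 264 and 792 all reproduce, and no section sets power to win on both formats as a target.

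Four further points also stand, wholly or in part.

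- The gain depends on both formats working. It is 0.1 point for the effective format if only one works, and nil for the chance of at least one success.
- The gain shrinks with the full sample. The plan analyses everyone randomized, and the Discussion says hospitalization and death are ascertained regardless of withdrawal. If all 264 per arm contribute at full effect, little is left to gain. However, the protocol added those patients because it expected discontinuation to cost power, and with a weaker second effect the gain for that format stays near 10 points.
- There is a trade-off. A sponsor comparing a USB device with a paper book may prefer each claim to rest on its own 2.5 % test. Holm weakens that, though it stays within the 5 % bound.
- Holm changes the verdict only when one p-value lies between 0.025 and 0.05, and there the 97.5 % interval includes no effect. Offering 97.5 % intervals as the companion to the test would therefore contradict it.

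A reader might also infer that Holm allows a smaller trial, since about 142 per arm gives 80 % power per comparison if both formats work. That does not follow. At 142 the fixed-split power is 75.1 %, and Holm adds almost nothing if only one format works.

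**Conclusion.** The point holds as an efficiency gain, not as an error. For the same implied 5 % family-wise level, Holm is never less powerful than the fixed split. Its benefit ranges from nearly nil (only one format works) through about 1.4 points per comparison and 3 points for both (264 per arm, full effect) to about 5 and 10 points (158 per arm, full effect in both).

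The power figures assume a 70 % control proportion, two-sided tests and the Fisher test used for sizing. The planned analysis is an Andersen-Gill model, for which the article gives no event-rate or overdispersion inputs, so its actual power cannot be computed from the documents. The direction does not depend on the test, because Holm works on whatever p-values the model yields. The 15 % effect is an assumption made for illustration.

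**What to change.** Before unmasking, replace the threshold sentence in *Primary statistical analyses* with: *The two co-primary p-values are tested by Holm's procedure at two-sided family-wise 0.05: the smaller at 0.025 and, if significant, the larger at 0.05.* Leave the sample size calculation at 0.025. This sentence also makes explicit the family-wise level and the sidedness, which the article now leaves implied.

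Make Holm-adjusted p-values the decision rule: twice the smaller p-value, and for the other comparison the larger of that figure and its own p-value. In the example, p = 0.001 and p = 0.04 become 0.002 and 0.04. Report 95 % and 97.5 % intervals alongside, labelled as not being the basis of the test decision.

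The cost is one sentence and a reporting note, with no extra patients or data. The sponsor should accept knowingly the higher chance of a false rejection for an ineffective format when the other works (about 4-5 % instead of 2.5 %) and the loss of a simple match between interval and test.
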